## **9. QUALITY ASSURANCE**

EXPLORATORY STUDY materials and quality assurance related to the imaging of participants and any involvement onsite at HIRF will take place as per existing HIRF/RBWH processes. Data quality will be considered and described in the presentation of results.

The MAIN study is a registered clinical trial employing an external study monitor responsible for quality assurance with respect to inoculum and participant safety (including pathology testing and clinical examination/investigations.)

## **10. STATISTICAL CONSIDERATIONS**

### **10.1 Sample Size**

This is a pilot investigation to assess the application of functional nuclear medicine in subpatent malaria. The population will comprise of two adults (male and female of non-childbearing potential) participants between 18 and 55 years of age, recruited from the IBSM model MAIN study population.

It is expected that this study will be hypothesis generating. There are no pre-existing PET or prospective MRI imaging trials in malaria published in the literature. Data from this pilot investigation may be used in future power calculations if required.

### **10.2 Statistical Analysis Plan**

All data will be presented descriptively. Pre and post inoculation quantitative imaging metrics will be compared with paired T-tests or Mann-Whitney U tests (statistical

significance  $p < 0.05$ ). Imaging results may be described with respect to demographic, clinical and biochemical data collected as part of the MAIN study.

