## **3. STUDY DESIGN**

This is an EXPLORATORY STUDY comprising a population recruited from a single-center, IBSM model MAIN study. This EXPLORATORY STUDY is a pilot investigation to establish the role of  $^{18}\text{F}$  FDG-PET/MRI in studying the pathophysiology of subpatent malaria. The population will consist of two healthy adults inoculated with *P. falciparum* from existing MAIN study population.

MAIN study refers to the parallel IBSM MAIN study QP15C20 SJ733

Participants will receive **two** whole body PET/MRI scans: the first within one week prior to MAIN study inoculation and the second one to two days prior to confinement with peak parasitaemia post BSP inoculation (estimated MAIN study InD 6 to 7). Blood samples will be collected at MAIN study timepoints.

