#### **Evaluation of data:**

All data will be presented descriptively. Pre and post inoculation quantitative imaging metrics will be compared with paired T-tests or Mann-Whitney U tests. Groups will be compared with unpaired T-tests with consideration of T-value adjustment for population size and Mann-Whitney U tests. Any groups identified based on imaging results will be described with respect to demographic, clinical and biochemical data collected as part of the MAIN study.

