## **10. STATISTICAL CONSIDERATIONS**

### **10.1 Sample Size**

This is a pilot investigation to assess the application of advanced medical imaging in subpatent malaria. The population will comprise of eight adults (male and non-pregnant, non-lactating female participants between 18 and 55 years of age, recruited from the IBSM model MAIN study population.

It is expected that this study will be hypothesis generating. There are no pre-existing PET or prospective MRI imaging trials in malaria published in the literature. Data from this pilot investigation may be used in future power calculations if required.

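### In the two-participant protocol (ACTRN12616001458426), the planned p<0.05 tests are uninformative at n=2: Mann-Whitney cannot reach the threshold, the paired t-test has 1 df, and the group t-test cannot be computed

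*Supplement*

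**What the plan says.** All quotations here are from the protocol registered as ACTRN12616001458426. It has its own registration and its own linked MAIN study, so it is the current plan for that study and not an earlier version of the eight-participant protocol ACTRN12616001238460.

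- Section 10.1 fixes the size: "The population will comprise of two adults".
- Section 3 gives each person two scans: "the first within one week prior to MAIN study inoculation and the second one to two days prior to confinement with peak parasitaemia".
- Section 10.2 opens with "All data will be presented descriptively" and continues: "Pre and post inoculation quantitative imaging metrics will be compared with paired T-tests or Mann-Whitney U tests (statistical" significance at p<0.05). It does not say how to choose between the two tests, or whether they are one- or two-sided.
- Section 3, under Evaluation of data, adds: "Groups will be compared with unpaired T-tests with consideration of T-value adjustment for population size and Mann-Whitney U tests". The study has one species and two people, and no groups are defined.
- Section 10.1 ends: "Data from this pilot investigation may be used in future power calculations if required".

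The companion protocol plans more people ("The population will comprise of eight adults"; its section 3 says up to eight) and has the same pre/post test sentence in its own section 10.2. Neither protocol says whether the two data sets will be combined or kept apart.

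**The concern.** A significance threshold is useful only if the test can cross it for reasons connected with the effect. With two pre/post pairs per metric, one of the two named tests can never cross it. The other can cross it only when two people happen to change by almost the same amount. Since no rule selects the test, that choice alone decides whether significance is possible. A non-significant result would say almost nothing about FDG uptake, and a significant one could be over-read.

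The second risk lies downstream. Section 10.1 allows these data to feed a later power calculation, and an SD of change from two people is too imprecise for that on its own.

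**Working it through.** The plan gives no effect size, SD or power, so it has no calculation to reproduce. The check is what the named tests can do at the stated size.

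**Inputs.** n = 2 participants (section 10.1), two scans each (section 3), threshold 0.05 (section 10.2). Two-sided testing is assumed because the plan does not say; one-sided values are also shown. Results in SD units assume normally distributed changes.

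**1. Mann-Whitney U on pre versus post.** This treats the scans as two independent samples of 2, which ignores the pairing.
- Smallest exact two-sided p = 2/C(2n, n) = 2/C(4, 2) = 2/6 = 0.33.
- One-sided: 1/6 = 0.17.
- Normal approximation, two-sided: 0.245 with continuity correction, 0.121 without.

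No variant reaches 0.05.

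**2. Paired t-test.** df = n − 1 = 1, and the critical |t| is 12.706. With changes d1 and d2, the mean is (d1 + d2)/2 and its standard error is |d1 − d2|/2, so

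|t| = |d1 + d2| / |d1 − d2|.

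If the signs agree and r is the larger change divided by the smaller, then p<0.05 requires (r + 1)/(r − 1) > 12.706. That gives r < 13.706/11.706 = 1.17. If the signs differ, |t| is below 1. One-sided, the critical value is 6.31 and the limit on r is 1.38.

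Two illustrations with assumed changes:

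| Changes | Mean change | t | p |
|---|---|---|---|
| 0.10 and 0.11 | 0.105 | 0.21/0.01 = 21 | 0.030 |
| 0.10 and 0.20 | 0.150 | 0.30/0.10 = 3 | 0.205 |

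The larger mean effect is the non-significant one.

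- 95% CI half-width = 12.706/√2 = 8.98 SD of change.
- Power at assumed true mean changes of 1, 2, 3 and 5 SD is 9%, 18%, 26% and 42%; 80% power needs about 11.5 SD.
- Under normality the test keeps its size: the simulated type I error was 0.049. Its fault is therefore lack of information, not an inflated error rate.

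**3. Unpaired group comparison (section 3).** Two people can be split into two groups only as 1 versus 1.
- t-test: df = 1 + 1 − 2 = 0, so it cannot be computed.
- Mann-Whitney: smallest two-sided p = 2/C(2, 1) = 1.0.

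**4. SD carried into a later power calculation.** The 95% limits, as multiples of the estimate, are √(df/χ²) at the 0.975 and 0.025 quantiles. With df = 1 they are 0.45 and 31.9. For comparison, n = 8 gives 0.66 to 2.04.

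**The case against.** The strongest defence is the framing. Both sections that name the tests begin by promising descriptive presentation, the study is called hypothesis generating, and no decision or stopping rule depends on a p-value. Reporting individual values already fits that promise. This stands, and it limits the seriousness. It also argues for removing the tests, since they add nothing to a descriptive aim.

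The group comparison appears only in section 3 and is absent from section 10.2, so it may be left over from other text. That is fair, but section 3 still commits to it, and the two sections should agree. Section 10.1 says only that the data may be used for power calculations, not that an SD from two people will be used alone. So that part of the point is a caution.

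Three stronger readings are tempting, and the documents do not support them:

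- **That no test can work, so a null result is certain.** The paired t-test is computable and reaches p<0.05 when the two changes are close enough.
- **That the two studies are planned as separate analyses.** This could be inferred from there being two protocols, but both are silent.
- **That a correlation of uptake with biomass would be forced to +1 or −1.** No correlation is specified. The plan says only that markers and uptake will be compared.

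**Conclusion.** The point holds for ACTRN12616001458426. The p<0.05 criterion cannot be met by Mann-Whitney (floor 0.33 exact two-sided; above 0.05 in every variant checked), and the 1 versus 1 group t-test cannot be computed. The paired t-test can meet the criterion only when two same-sign changes lie within a factor of 1.17 of each other. Its 95% CI half-width of 9.0 SD shows how little it can say about the size of the effect.

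The exact Mann-Whitney floor, the degrees of freedom and the 1.17 limit follow from n = 2 and the 0.05 threshold, two-sided for the 1.17 limit. The power figures, the coverage of the CI and the SD limits also rest on normality, which two values cannot check. The SD multiples used for power are assumptions, because the documents give no SD.

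This is a wording correction to a descriptive pilot. It does not invalidate the study or its scans.

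**What to change.** In ACTRN12616001458426, delete the paired t-test, the Mann-Whitney test and the p<0.05 threshold from sections 3 and 10.2, and delete the unpaired group comparison from section 3. In their place, report each participant's pre value, post value and change for every region of interest. Replacing Mann-Whitney with the paired rank test would not rescue the testing: the signed-rank floor at n = 2 is 2/2² = 0.50. Add to section 10.1 that an SD of change from these two people will not be used alone for a future sample size. The cost is wording only, with no extra scans or participants.

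Optionally, state in advance in both protocols whether the two studies will be combined, so that the choice is not made after results are seen. A pooled analysis should use a paired method and show results by species. At the ceiling of 10 people the 95% CI half-width would be 2.262/√10 = 0.72 SD, with SD limits of 0.69 to 1.83 times the estimate, if one SD of change holds throughout.

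That assumption is a real trade-off. The companion study admits P. vivax, scanned at an estimated InD 8 to 9 rather than 6 to 7, draws on more than one MAIN study, and enrols only up to eight. Pooling is therefore a choice to declare, not a necessary part of the correction.

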## **11. SOURCE DOCUMENTS AND ACCESS**

Upon request, the investigator(s)/institution(s) will permit direct access to source data/ documents for trial-related monitoring, audits, HREC review, and regulatory inspection(s) by the Sponsor (or their appropriately qualified delegate) and Regulatory Authorities provided this is feasible from a technical standpoint. Direct access includes examination, analysis, verification and reproduction of records and reports that are important to the evaluation of the study.

## **12. ADMINISTRATIVE PROCEDURES**

### **ETHICAL CONSIDERATIONS**

The amount of blood to be sampled in the study is not considered to be excessive in healthy adult participants. This study will be carried out according to the Declaration of Helsinki, the NHMRC National Statement on Ethical Conduct in Human Research (2007) and the Notes for Guidance on Good Clinical Practice as adopted by the Australian Therapeutic Goods Administration (2000) (CPMP/CH/135/95) and the ICH GCP Guidelines.

### **ETHICAL REVIEW COMMITTEE**

This Protocol will be submitted for approval to QIMR-B HREC, Clinical Trial Protocol Committee. This protocol will then be submitted for executive approval from RBWH HREC. Following this the HIRF Scientific Advisory Committee will review the Protocol and QIMR-B HREC assessment(s) in order to facilitate expedited Site-Specific Approval from the RBWH/Metro North HREC.

Written approvals will be obtained before volunteers are recruited and participants are enrolled. The Investigators will receive all the documentation needed for submitting the present Protocol to the HREC.

It is the responsibility of the Investigator to report study progress to the HREC as required or at intervals not greater than one year.

An earlier version of this protocol was submitted to the QIMR Clinical Trials Protocol Committee and was referred for review by the Human Scientific Sub-Committee on the grounds that the proposed study is not a clinical trial. Subsequent discussion with the TGA and study sites have established that the HREC review process described above is required to meet the regulatory requirements for research using the standard radiotracer  $^{18}\text{F}$  FDG and between the nominated sites.

### **REGULATORY AUTHORITIES**

This is an EXPLORATORY STUDY to run in parallel to an existing MAIN study clinical trial. The investigation uses the application of imaging using a standard radiotracer at standard dosages that is widely used in the clinical setting. This is administered as per existing local institution processes. Due to the unique nature of radiopharmaceuticals, facilities are able to extemporaneously produce and administer FDG onsite for their own purposes. The RBWH Nuclear Medicine department has TGA approval for manufacture of this radiotracer (Appendix F). This radiotracer is not ARTG listed for this facility, but is approved for GMP production and commercial sale from this manufacturer to other facilities within the state of

Queensland. Following discussion with the TGA and study sites, this EXPLORATORY STUDY has a CTN registration for the **regulatory purpose** of accessing the standard radiotracer  $^{18}\text{F}$  FDG in a manner that ensures prospective record keeping and transparent usage. This includes processes for AE reporting as documented below.

An independent nuclear medicine medical advisor has been nominated to ensure participant safety, to provide advice and ongoing review of any SAEs that may be related to this EXPLORATORY STUDY activities. No DSMB has been nominated given the low risk nature of this small population EXPLORATORY STUDY. Participants will receive a copy of a current FDA template for  $^{18}\text{F}$  FDG product information (Appendix G), as no generic equivalent exists in Australia.

#### INFORMED CONSENT

Before recruitment and enrolment into the study, each prospective participant must be given a full explanation of the nature and purpose of the study, and a copy of the Participant Information Sheet and Consent Form to review. This form complies with the consent form requirements outlined in the TGA guidelines. Once the essential study information has been provided, and the Investigator is assured that each individual volunteer understands the implications of participating in the study, the participants will be asked to give consent to participate in the study by signing the informed consent form. The consent form shall be signed and dated by the appropriate parties. A notation that written informed consent has been obtained will be made on the participants' MAIN study file. The completed consent forms will be retained by the Investigator and a copy of these will be provided by the Investigator to the participant.

#### PARTICIPANT RE-IMBURSEMENT

Participants who are found eligible and complete the study will be compensated \$160 for their time. This is in addition to MAIN study compensation.

#### EMERGENCY CONTACT WITH INVESTIGATORS

All participants will be provided with a Participant Information Sheet and Informed Consent Form with contact details of whom to contact in the case of an emergency related to the EXPLORATORY STUDY.

Participants will also be provided with a contact card as per the MAIN study.

#### NOTIFICATION OF PRIMARY CARE PHYSICIAN

Where it is deemed appropriate by the investigator(s), study doctor and/or reporting radiologist a letter will be sent to the physician stating the nature of the EXPLORATORY STUDY including any adverse events or incidental findings. A copy shall be retained by the study site as part of the MAIN study participant file.

### PROTOCOL DEVIATIONS

All protocol deviations must be reported to the principal investigator. Protocol deviations will be assessed for significance by the principal investigator. Those deviations deemed to have a potential impact on the integrity of the study results, patient safety or the ethical acceptability of the trial will be reported to the HREC prior to completion of participant enrollment. Where deviations to the protocol identify issues for protocol review, the protocol may be amended as above.

### RETENTION OF OTHER STUDY SPECIFIC SAMPLES

Electronic imaging data will be retained as per HIRF guidelines. No other samples will be collected.

### INSURANCE AND INDEMNITY

This EXPLORATORY STUDY is an observational study to run parallel with existing MAIN study clinical trials. There are no specific expected SAEs from participation requiring indemnity, however in the event of an AE that is deemed related to EXPLORATORY STUDY participation (following Investigator and medical monitor review) the sponsor holds No-Fault Compensation for Clinical Trials insurance policy for this study. The site HIRF is part of the RBWH campus.

The MAIN study holds a No-Fault Compensation for Clinical Trials insurance policy.

### FINANCIAL DISCLOSURE AND CONFLICT OF INTEREST

Nil conflicts of interest identified or disclosed.

## **13. DATA HANDLING, RECORD KEEPING AND PUBLICATION POLICY**

### DATA CONFIDENTIALITY

Only the investigators, designated staff and designated MAIN study staff will have access to information that identifies a study participant.

All MAIN study participants will be assigned a unique identifier.

Participant identifiers in this EXPLORATORY STUDY will be consistent with those used in corresponding MAIN studies.

### DATA CAPTURE METHODS

All imaging data will be collected in accordance with site-specific HIRF protocols.

### TYPES OF DATA

Imaging data, reports and quantitative imaging metrics will be electronically stored in accordance with HIRF guidelines.

### RECORD KEEPING

All study related documents and records are to be retained for a minimum of fifteen years after MAIN study completion. Written agreement from the Sponsor must precede destruction of the same. In cases where HIRF guidelines preclude the storage of source imaging data, data will be transferred to the sponsor for storage.

## PUBLICATIONS POLICY

Publication and reporting of results and outcomes of this trial will be accurate and honest, undertaken with integrity and transparency and in accordance with QIMR BERGHOFER's Policy on Criteria for Authorship. Publication of results will be subjected to fair peer-review. Authorship will be given to all persons providing significant input into the conception, design, execution or reporting of the research according to QIMR BERGHOFER Policy on the Criteria for Authorship.

**ACTRN12616001238460 linked to IBSM study ACTRN12616000174482**

## **PROTOCOL SYNOPSIS**

**Full Title:** Advanced medical imaging in subpatent malaria: a pilot study

**Short Title:** NA

### **Objectives:**

Primary:

- To investigate the use of  $^{18}\text{F}$  FDG-PET/MRI to estimate the biodistribution of *Plasmodium* species in human volunteer induced blood stage malaria studies.
- To investigate the use of  $^{18}\text{F}$  FDG-PET/MRI to estimate the biomass of *Plasmodium* species.

Secondary:

- To describe the relative burden of organ-specific tissue sequestration in *Plasmodium* species.
- To describe the impact of early malaria infection on glucose metabolism.
- To describe the MRI brain findings of early malaria infection in a prospective participant cohort.

**Population:** Eight adult (male and non-lactating, non-pregnant female) participants between 18 and 55 years of age, recruited from induced blood stage malaria (IBSM) model MAIN study populations under QIMR-Berghofer sponsorship.

**Phase:** exploratory

### **Description of Investigation:**

Participants will receive a whole body PET/MRI scan and dedicated MRI scan within roughly one week prior to inoculation and on one to two days prior to confinement with peak parasitaemia post BSP inoculation (estimated InD 6 to 7 for *P. falciparum* and InD 8 to 9 for *P. vivax*). Preparation for PET/MRI imaging involves fasting for 6 hours prior, abstaining from excessive physical exertion and following a low carbohydrate diet 24 hours prior (recorded on a diet and activity sheet). PET/MRI scans will be performed on the Biograph mMR PET/MRI system after the intravenous infusion of the standard radiotracer 2- $(^{18}\text{F})$  fluor-deoxy-D-glucose(FDG) ( $^{18}\text{F}$  FDG) and dedicated MRI scans on the MAGNETOM Prisma 3T MRI system. Collected images will be reviewed and reported by experienced radiologists specialising in MRI and nuclear medicine reporting. Quantification of  $^{18}\text{F}$  FDG uptake measurements will be established for intra-individual scans using Patlak model analysis and semi quantitative SUV measurement with reference to an  $^{18}\text{F}$  FDG external control.

**Study Duration:** October 2016 – June 2017

**Participant Participation Duration:** Estimated 8-14 days

**Estimated Time to Complete Enrollment:** August 2016 – March 2017

|                                                                            |           |
|----------------------------------------------------------------------------|-----------|
| 1. KEY ROLES AND CONTACT INFORMATION .....                          | 9  |
| 1.1 Study Location(s) .....                                                | 10        |
| 1.2 Study Management.....                                                  | 10        |
| 2. INTRODUCTION: BACKGROUND AND SCIENTIFIC RATIONALE.....           | 11 |
| 2.1 Background Information .....                                           | 11        |
| 2.2 Study Objectives .....                                                 | 12        |
| 3. STUDY DESIGN .....                                               | 14 |
| 3.1 Study Flow Chart.....                                                  | 16        |
| 4. PARTICIPANT ENROLLMENT AND WITHDRAWAL .....                      | 16 |
| 4.1 Recruitment.....                                                       | 16        |

## **2. INTRODUCTION: BACKGROUND AND SCIENTIFIC RATIONALE**

### **2.1 Background Information**

Morbidity and mortality from malaria infection remains significant despite anti-parasitic treatments. Understanding the pathophysiology of disease may aid in the development of adjunctive therapies to improve survival in severe cases. Parasite sequestration in tissue microvasculature permits evasion of the reticulo-endothelial system and increased biomass [1]. Organ specific sequestration contributes to end organ dysfunction in severe malaria syndromes. Owing to the inaccessibility of sequestered parasites, estimations of total biomass and sites of sequestration have historically relied on biochemical markers [2-5], animal models [1, 6, 7] and post mortem studies [8]. Determination of the biodistribution of malaria with functional nuclear medicine imaging may allow for more direct study of sequestration in human models. This may aid developing a better understanding of the organ dysfunction experienced in severe cases.

Nuclear medicine imaging techniques, particular hybrid PET/CT and PET/MRI have a central role primarily in oncology for assessing the biodistribution and activity of malignancy. The ability of these techniques to detect and locate biological and biochemical changes have more recently been applied to other medical fields including Infectious Diseases, though there are no studies in malaria.

Other advanced imaging techniques including dedicated MRI imaging have been successfully applied to examine the pathophysiology of malaria, predominately in patients presenting with severe disease. There are few studies in early or uncomplicated infection, and none of these studies have been prospective. As a result there remains a paucity of imaging data in the early stages of infection.

This EXPLORATORY STUDY has been designed as a prospective pilot investigation to establish the role of  $^{18}\text{F}$  FDG-PET/MRI and advanced dedicated MRI imaging techniques in studying the pathophysiology of subpatent malaria following low dose *Plasmodium* exposure in healthy adults. Collection of baseline and post inoculation

PET/MRI imaging will provide information about changes in host/parasite glucose metabolism that may be used to estimate parasite biomass and biodistribution. Glucose uptake is increased up to 100-fold in parasitised erythrocytes [9], suggesting that  $^{18}\text{F}$  FDG may be a viable radiotracer to help evaluate the disease.

Whole body PET/MRI is a functional imaging modality that provides detailed soft tissue anatomical information with lower ionizing radiation exposure compared to equivalent PET/CT. The radiotracer  $^{18}\text{F}$  FDG is a safe and well-validated biomimetic for demonstrating glucose uptake. Imaging with  $^{18}\text{F}$  FDG-PET/MRI is an ideal model for exploring nuclear medicine functional imaging in a healthy human volunteer population.

Biochemical estimates of parasite biomass and parasitaemia will be compared to quantified radiotracer uptake measurements. Comparison of interval changes in host/parasite glucose metabolism will add to our understanding of the metabolic changes associated with disease [10]. The feasibility of  $^{18}\text{F}$  FDG-PET/MRI may contribute to developing a further role for nuclear medicine imaging in malaria.

Dedicated MRI imaging can demonstrate inflammation other subtle metabolic changes, including changes in vascular function. Comparison of interval changes in dedicated MRI imaging will add to our understanding of early disease progression and permit comparison with the existing literature in more advanced disease.

Successful application of advanced medical imaging would provide a greater understanding of parasite sequestration dynamics, which may aid in disease modeling and development of treatments to prevent end organ damage in severe disease.

